#### Inclusion criteria

2.4.1

Participants will be included if they meet the following criteria: (1) Patients with a first-ever ischemic or hemorrhagic stroke, meeting the stroke diagnostic criteria established by the fourth National Conference on Cerebrovascular Disease of China in 1995, and confirmed by computerized tomography (CT) or magnetic resonance imaging (MRI); (2) Adults, aged 30–70 years old; (3) Within 6 months of stroke onset; (4) The disease is stable, neurological conditions and vital signs are no longer progressing; (5) The ability to sit independently for approximately 40 min to finish the treatments and assessments, including preparing time; (6) Without visual impairment, able to see the content of the experiment program; (7) Unilateral limb hemiplegia, Brunstrom Recovery Stages for Upper Extremity 3, 4, or 5 stage at the time of enrollment; (8) Right-handed, determined by the Edinburgh Handedness Inventory (EHI) – Short Form (28); (9) Chinese speaking; (10) Junior high school education or above; and (11) Willingness to provide informed consent and comply with the study protocol.

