### Outcomes

2.7

All participants will be evaluated by clinical scales, fNIRS, and sEMG before and after 4 weeks of interventions. At baseline, sociodemographic and neurologic data will be collected, including age, gender, Body Mass Index, education, medical history, type of stroke, location of injury, and duration of disease. In addition, questionnaire surveys about safety, satisfaction, and feedback will be performed at the end of the interventions. Adverse events and serious adverse events will be monitored from the beginning to the end of the study. Expert therapists with above 10 years of experience will conduct the functional measures.

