#### Secondary outcomes

2.7.2

Brunstrom Recovery Stages for Upper Extremity will be used to assess severity of the deficits post stroke, it has good reliability and validity (35). Manual Muscle Test will be conducted on the key upper extremity and hand muscles. Passive and active range of motion will be measured of the key upper extremity and hand joints. The Modified Barthel Index is a 10-item scale with good reliability and validity, it is used to assess the patient’s ability to perform ADLs (36). The Functional Independence Measure will be used to measure the ability to carry out everyday tasks safely and independently, thus to determine burden of care, it’s reliability and validity are excellent (37).

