### Sample size

2.10

The primary outcome of this study is FMA-UE. A power analysis of the independent sample t-test was conducted using R package pwr version 1.3.0. According to a previous study, the effect size (d) was set at 0.8, the significance level was 0.05, and the power was 0.85; the calculated sample size was 60 participants in total, 30 participants in each group (43). Based on a dropout rate of 5%, it is estimated that 32 participants need to be recruited in each group.

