### Statistical analysis

2.12

For continuous variables, Shapiro–Wilk normality tests will be performed to assess their normality. Data following normal distribution will be expressed as mean ± standard deviation (SD), while the non-normal distributed data will be described as median and interquartile range (IQR). If each group’s data conforms to normal distribution and homogeneity of variance, the independent sample *t*-test will be used to compare the inter-group difference, and the paired *t*-test will be used to compare the intra-group difference pre- and post-interventions. If the data does not conform to normal distribution and homogeneity of variance, the non-parametric tests will be used for comparisons between and within groups. The categorical variables will be expressed as frequency and percentage; Chi-square test will be used for comparison between and within groups. Pearson or spearman correlation analysis will be used to test the correlation between variables according to their distributions. The significance level will be set as *α* = 0.05. We will use R version 4.2.3 and RStudio version 2024.04.21 (Posit Software, MA) to conduct the statistical analysis (44).

All the analyses will be conducted based on the Intention-To-Treat principle. For participants who quit the study midway, a subgroup analysis will be conducted with the collected outcome data. After the first 20 participants have finished all the evaluations, an interim analysis will be conducted according to the statistical analysis plan.

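### The chi-square test named for within-group categorical comparisons ignores that the before and after measurements come from the same patients

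*Protocol article*

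**What the plan says.** Section 2.12 (Statistical analysis) treats the two data types differently.

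- Continuous variables, when normality and equal variance hold: an independent t-test between groups, and a paired t-test that "will be used to compare the intra-group difference pre- and post-interventions".
- Continuous variables otherwise: "the non-parametric tests will be used for comparisons between and within groups", with no test named.
- Categorical variables: "Chi-square test will be used for comparison between and within groups".

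Section 2.7 (Outcomes) fixes the measurement times: "All participants will be evaluated by clinical scales, fNIRS, and sEMG before and after 4 weeks of interventions". Two secondary outcomes in section 2.7.2 are recorded as grades or stages: "Brunstrom Recovery Stages for Upper Extremity will be used to assess severity of the deficits post stroke", and "Manual Muscle Test will be conducted on the key upper extremity and hand muscles". Neither there nor in section 2.12 is any outcome assigned to the continuous or the categorical class.

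**The concern.** In section 2.12 a within-group comparison means the same patients before and after treatment. The paired t-test shows that the plan recognises this for continuous data. For categorical data one unqualified test serves both the between-group and the within-group comparison, and no paired categorical test appears anywhere in the article.

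An ordinary chi-square test can be laid out on such data in two ways, and neither answers the question of change:

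- **Time by category.** Each patient is counted twice, as if 30 patients were 60 independent people. When a patient's two results are positively correlated, the test is conservative and real change is missed.
- **Before by after.** The test asks whether the baseline category is associated with the final one. That is usually so, whether or not anyone has improved.

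At stake are the within-arm p-values for whichever outcomes are handled as categorical.

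**Working it through.** **Inputs.** The Sample size section gives 30 patients per group. Reproducing it: "the effect size (d) was set at 0.8", alpha 0.05 (two-sided assumed) and power 0.85 give 29.05, rounded up to 30; 30/(1 − 0.05) = 31.6, rounded up to 32. The plan's figures reproduce and are used here only to fix the number per arm. The Inclusion criteria give "Brunstrom Recovery Stages for Upper Extremity 3, 4, or 5 stage at the time of enrollment". Equal baseline shares, gain and loss rates, correlations and shifts below are assumptions.

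**1. Worked example, time by stage.** Ten patients each start at stages 3, 4 and 5, and three from each stage move up one (9 of 30 gain, none lose).

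| Stage | 3 | 4 | 5 | 6 |
|---|---|---|---|---|
| Before | 10 | 10 | 10 | 0 |
| After | 7 | 10 | 10 | 3 |
| Expected in each row | 8.5 | 10 | 10 | 1.5 |

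- Unpaired chi-square: 2 × 1.5²/8.5 + 2 × 1.5²/1.5 = 0.529 + 3.000 = 3.53 on 3 df, p = 0.32.
- Paired but unordered (Bowker, over the three occupied pairs of cells): 3 × (3 − 0)²/(3 + 0) = 9 on 3 df, p = 0.029. Stuart-Maxwell also gives 9 on 3 df.
- Paired and ordered (exact sign test, 9 against 0): 2 × 0.5⁹ = 0.004.

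Restoring the pairing moves p from 0.32 to 0.029. Using the order of the stages moves it on to 0.004.

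**2. Binary example, where order plays no part.** 10 of 30 before and 17 of 30 after, 7 up and 0 down. Pearson chi-square is 3.30, p = 0.069 (0.119 with continuity correction). Exact McNemar: 2 × 0.5⁷ = 0.016.

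**3. Simulated power**, 30 patients, 4,000 runs per setting, one-stage moves:

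| Gain / loss | Chi-square, time by stage | Sign test |
|---|---|---|
| 30% / 0% | 6% | 92% |
| 40% / 5% | 22% | 82% |
| 50% / 5% | 47% | 95% |

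Repeat runs move these by about one percentage point.

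**4. A second model**, with a latent normal variable cut into three ordered categories and n = 30. The power columns assume a true shift of 0.4 SD.

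| Before-after correlation | Chi-square type I error at nominal 0.05 | Chi-square power | Signed-rank power |
|---|---|---|---|
| 0.5 | 0.024 | 0.15 | 0.41 |
| 0.7 | 0.011 | 0.12 | 0.54 |
| 0.9 | 0.002 | 0.06 | 0.80 |

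The signed-rank test holds a type I error of 0.048 to 0.049 throughout. At zero correlation chi-square is at 0.050, so the shortfall comes from the pairing.

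**5. Before-by-after cross-table.** If nobody changes stage, the table is diagonal (10, 10, 10) and chi-square = 30 × 2 = 60 on 4 df, p = 2.9 × 10⁻¹². In a binary table with 8 and 18 unchanged and 2 moving each way, chi-square is 14.7, p = 0.0001, while McNemar gives p = 1.0.

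**The case against.** **The sentence may govern few outcomes, or none.** The article never calls Brunnstrom stage or muscle grade categorical. If they are scored as numbers they fall under the unnamed non-parametric route, where a signed-rank test would be a proper choice. FMA-UE, range of motion, Modified Barthel Index and Functional Independence Measure are scores or measurements, and the 4.25-point responder hypothesis compares groups. This stands, and it makes the point about those two scales conditional.

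**Chi-square could be shorthand for McNemar, Bowker or Stuart-Maxwell**, and an analysis plan that is not shown may say so. This is possible but strained: the same unqualified test is named for between-group use, and the section does write paired for the t-test. An unseen plan excuses detail left out of an article, but here a test is named. If that plan names a paired test, the two documents need reconciling.

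**The power gap mixes two faults.** The chi-square test ignores order as well as pairing, the rates are assumed, and a setting without losses favours the sign test. This stands. Hence all three settings are shown, along with the paired unordered result of 0.029 and the binary example.

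**Within-arm p-values do not carry the trial's claim.** This also stands. The hypothesis is superiority between groups, and a correctly paired within-arm test would still not show a treatment effect.

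**Conclusion.** The rule is wrong as written for paired categorical data, and the consequence is minor. Any outcome compared within an arm as categorical would get an invalid p-value. On a time-by-category table with positively correlated results the test is conservative: under the assumptions above, power is about 6% to 47% where a sign test has 82% to 95%, with part of the gap due to ignored order. On a before-by-after table it does not test change at all, though nothing in the article shows that this layout is intended.

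A reader might infer more than the article supports:

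- That the Brunnstrom and muscle-grade results will be wrong. Their data type is not stated, so they would be wrong only if analysed as categorical.
- That nearly all sensitivity is lost. That fits the 30%/0% setting, but not the 47% power at 50%/5%.
- That the efficacy conclusion is at risk. The FMA-UE analysis, the between-group comparisons and the sample size do not use this rule.

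**What to change.** In section 2.12, and in the analysis plan if it repeats the rule:

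- Keep the chi-square test for between-group comparison of unordered categories only.
- For within-group comparison, name exact McNemar for binary variables, and a Wilcoxon signed-rank, sign or marginal homogeneity test for ordinal grades.
- State whether Brunnstrom stage and muscle grade are analysed as ordinal or as numeric scores.
- Report, for each arm, how many patients moved up, stayed the same or moved down.

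The cost is a sentence or two of text. No new data, visits or patients are needed, and the sample size does not change.

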**Discussion:**

Applying VR in AO therapy (AOT) has become popular, another study direction to improve AOT is to combine it with peripheral stimulations simultaneously. Due to its full immersive characteristic and multi-sensory input, 360° videos based VRAO+NMES could improve the motivation and engagement level of participants. In addition, fNIRS and sEMG test results may act as good biomarkers to predict rehabilitation outcomes, helping select suitable candidates for this new intervention.

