Due to the effects of action visual stimulation on MNS and ES on motor units (MUs), VRAO+NMES may be helpful to accelerate the process of motor learning. In addition, the enhanced multisensory interactions generated by VRAO+NMES have potential to improve the alteration of body ownership and induce self-body recognition (23). To investigate the potential neuromuscular control mechanism underlying this new intervention, we will use functional near-infrared spectroscopy (fNIRS) and surface electromyography (sEMG) to evaluate the activation of brain regions and muscles, respectively. In addition, MNS network-based neuroplasticity changes have been confirmed recently, we will also explore the brain functional connection changes before and after the interventions (25).

We, therefore, aim to determine whether a concurrent application of VRAO and NMES would result in significant improvements in behavioral assessments and neurophysiological parameters, and to test whether the changes in motor function evaluated by clinical scales are related to the brain functional imaging results measured by fNIRS. We hypothesize that VRAO+NMES is superior in improving upper extremity and hand motor functions, ADLs, and MNS cortical activation levels compared to conventional therapy plus NMES. The underlying mechanism may be that the brain-muscle synchronous intervention enhances activation of the MNS and recruitment of MUs, thereby promoting brain plasticity changes, improving neuromuscular control function, and enhancing therapeutic effects.

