##### Task fNIRS data preprocessing and analysis

2.7.3.2

The task related fNIRS data will be analyzed by the NIRS Brain AnalyzIR Toolbox (40). Firstly, the task related fNIRS raw data (light intensity) will be converted into optical density. Secondly, Hb concentration changes will be calculated according to the mBLL (41). Thirdly, the autoregressive iteratively reweighted least squares (AR-IWLS) general linear model (GLM) algorithms will be used to quantitatively analyze the relationship between brain signal and stimulus, the regression coefficient (*β*) will be calculated. Fourthly, the linear mixed-effect model will be used in the group-level analysis, the estimated value of β and its corresponding standard error will be calculated, treating participants as random effects. The false discovery rate (FDR) method will be used to obtain multiple comparison correction *p*-values (P_FDR_) (42). Fifthly, after channel level data analysis, based on the probability registration method, the activation results of each region-of-interest will be obtained. Finally, the brain activation results will be visualized on the Colin27 standard brain (21).

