An important study trend is the potential use of VR in MNS-based rehabilitation treatments, especially in early neurorehabilitation or patients with severe motor deficits who cannot take part in voluntary therapeutic exercises (52). During AO or synchronous AO+MI, patients need to perceive and comprehend the observed actions, which include motor related cognitive processes. These treatments require attention, concentration, memory, language, problem solving, and executive functions, which all influence the learning process and clinical efficacy (12). What’s more, compared with 2D video observation, the cognitive load of using a VR headset is relatively high; participants need to maintain concentration and keep cognitive effort to view the videos during the interventions and assessments. Therefore, a key factor to influence the design of VR rehabilitation programs is to keep the patient attentive in an engaging and tailored environment during the VR training (53).

The findings of the mechanism sub-study part of this research will provide evidence for the increased neural activity induced by synchronous central and peripheral stimulations, thus to support a variety of interventions aimed at carrying out stimulations on both the central and peripheral levels. Some published studies supported this theory. For example, a study concluded that TMS+NMES could enhance the activities of primary motor cortical networks and sensorimotor peripheral circuits (54). In another study, MI+ES showed excellent effectiveness to improve upper extremity motor function in patients with severe paralysis (55). What’s more, as objective quantitative indicators, fNIRS and sEMG test results may act as good biomarkers of brain and muscle activations. These results can be used to predict rehabilitation outcomes, set realistic rehabilitation goals, confirm optimal treatment time window, choose best training intensity or dosage, and select suitable candidates for this new intervention.

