## Conclusion

4

The results of this study will provide evidence for the feasibility and potential clinical efficacy of a new innovative rehabilitative approach VRAO+NMES in stroke rehabilitation. This will promote its clinical applicability and generalize the use of this potentially promising approach in hospital, community and home rehabilitation settings. The fNIRS and sEMG sub-study results may provide biomarkers to predict motor function recovery and rehabilitation outcomes after stroke. These biomarkers may also be helpful to screen patients who are suitable to use this new kind of rehabilitation intervention, thus to help to select best candidates.

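### The stated correlation for the motor–fNIRS aim does not account for treatment arm, and no stated analysis supports using fNIRS or sEMG to select candidates for VRAO+NMES

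*Protocol article*

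**What the plan says.** The Introduction of the protocol article sets as an aim "to test whether the changes in motor function evaluated by clinical scales are related to the brain functional imaging results measured by fNIRS". The same paragraph hypothesises that the experimental arm will do better on upper-limb function and on mirror-neuron-system activation.

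The method for association is one sentence in section 2.12: "Pearson or spearman correlation analysis will be used to test the correlation between variables according to their distributions". The variables and time points are not named, and nothing says whether the arms are combined, analysed separately or adjusted for.

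The uses foreseen for the markers go further than association:

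- Abstract, Discussion: "fNIRS and sEMG test results may act as good biomarkers to predict rehabilitation outcomes, helping select suitable candidates for this new intervention".
- Section 3: "These results can be used to predict rehabilitation outcomes, set realistic rehabilitation goals". The same sentence goes on to the treatment time window, to "choose best training intensity or dosage", and to candidate selection.
- Section 4: "These biomarkers may also be helpful to screen patients who are suitable to use this new kind of rehabilitation intervention".

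Two other passages come near the subject but do not link a marker to outcome. In section 2.7.3.2, "the linear mixed-effect model will be used in the group-level analysis" concerns task activation, not FMA-UE. The subgroups in section 2.4.2 are defined by type of stroke and by size and site of the lesion, not by fNIRS or sEMG.

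**The concern.** There are two separate problems.

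First, if treatment shifts both FMA-UE and the marker, as the Introduction expects, patients in the experimental arm tend to be higher on both. A correlation over all patients is then positive even if, within each arm, the marker says nothing about recovery. The mechanism aim could appear met merely because the arms differ, and the risk grows with the treatment effect.

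Second, selecting candidates for VRAO+NMES requires evidence that the benefit over control depends on the marker. A bivariate correlation shows at most that the marker goes with outcome. A marker of natural recovery, equally informative in both arms, would pass that test and could be reported as a tool for choosing patients for this intervention.

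**Working it through.** **Inputs from the protocol article.** FMA-UE effect d = 0.8, α = 0.05, power 0.85, 30 per group, 5% dropout (section 2.10); 1:1 allocation (section 2.1). A two-sided test is assumed.

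**Inputs assumed.** The documents give no arm effect on any fNIRS marker, so 0 to 1.6 SD is shown. The d of 0.8 is applied to the FMA-UE measure used in the correlation. Data are normal with unit within-arm SD.

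**Step 1: the plan's own figure.** The two-sample t-test needs 29.05 per group, so 30 (power 0.861 at 30). Then 30/0.95 = 31.6, so 32. Both stated figures reproduce.

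**Step 2: correlation created by the arm difference.** With zero within-arm correlation and equal arms, the difference adds dx·dy/4 to the covariance and d²/4 to each variance:

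r = (dx·dy/4) / √[(1 + dx²/4)(1 + dy²/4)]

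For dx = dy = 0.8: r = 0.16/1.16 = 0.14. Fisher's z gives atanh(0.138)·√57 ≈ 1.05, so the rejection rate is Φ(1.05 − 1.96) + Φ(−1.05 − 1.96) ≈ 18%.

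Simulation at 30 per arm with dy = 0.8 (40,000 trials; 10,000 for Spearman) gives these rates of p < 0.05 when no within-arm relation exists:

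| Assumed marker shift (SD) | Induced r | Pooled Pearson | Pooled Spearman | Adjusted for arm |
|---|---|---|---|---|
| 0 | 0.00 | 5.0% | 5.0% | 5.1% |
| 0.5 | 0.09 | 10.6% | 10.2% | 5.1% |
| 0.8 | 0.14 | 18.4% | 17.3% | 4.8% |
| 1.2 | 0.19 | 31.4% | 32.4% | 5.1% |
| 1.6 | 0.23 | 44.3% | 45.5% | 5.1% |

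The first row is the case of a baseline marker: randomisation makes its expected arm difference zero, and the test keeps its level.

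**Step 3: prognosis is not selection.** Take a baseline marker with an assumed r = 0.5 with outcome in both arms, d = 0.8 on outcome and 30 per arm (4,000 trials). The pooled correlation is significant in 96% of trials. The arm-by-marker interaction is significant in 4.6%, its null rate, as it should be for a marker that does not distinguish who benefits.

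**Step 4: what an interaction could detect.** Comparing correlations between arms by Fisher's z, the standard error is √(2/27) = 0.272 at 30 per arm. For assumed correlations of 0 and 0.5, atanh(0.5)/0.272 = 0.549/0.272 = 2.02, giving power Φ(2.02 − 1.96) ≈ 52%. For 0 against 0.6 it is 72%, and for 0 against 0.7 it is 89%. If signal screening (section 2.7.3) left, say, 24 per arm, these would be 43%, 61% and 80%.

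**The case against.** A reader might infer that the plan pools the arms. It does not say so. Section 2.12 checks distributions by group and makes comparisons both between and within groups, so separate correlations by arm fit the text equally well. They would remove the artefact of step 2. They would not show whether the benefit over control depends on the marker, so the second problem remains.

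A reader might also infer that pooling undermines the biomarker claims generally. It does not: a marker used to screen patients would naturally be measured at baseline, where the pooled test holds 5%. The inflation concerns change or post-treatment measures, which are the subject of the aim in the Introduction.

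The marker shifts are assumptions. Section 2.7.3 lists both video conditions in the fNIRS task. If every participant performs both, an arm difference would reflect four weeks of training, not the video on screen, and a large shift cannot be presumed. This is why a range is shown.

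Most of the biomarker wording is hedged, appears outside the methods, and is not a stated hypothesis; section 3 is firmer in saying that the results can be used. Arm handling may also be settled in an analysis plan that is not shown, and silence on it would not by itself be a finding. What stands is that the one method stated does not fit the uses described.

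Finally, it is tempting to say that neither time window nor dosage varies in the trial. That is right only for dosage: section 2.6 gives both groups the same schedule. Time since onset does vary, because section 2.4.1 admits patients at any point in the first six months and section 2.4.2 records the timing. It is simply not assigned.

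**Conclusion.** The point holds for a stated method that does not match its stated purpose. If the arms are combined without adjustment, a change or post-treatment marker unrelated to recovery within arms would be declared related in about 11% to 31% of trials, against a nominal 5%. This rests on assumed marker shifts of 0.5 to 1.2 SD, the planned FMA-UE effect of 0.8 SD, and 30 analysed per arm. With no shift there is no inflation.

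Independently of those assumptions, neither a pooled nor a by-arm correlation can identify who benefits from VRAO+NMES, and no marker-by-arm analysis is described. The candidate-selection wording in the Abstract and in sections 3 and 4 is therefore unsupported, and the claim about training intensity or dosage cannot be addressed by this design. The primary comparison of FMA-UE between arms is not affected.

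**What to change.** For the aim of relating motor change to fNIRS:

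- Name the markers and time points. Replace the simple correlation by a regression of 4-week FMA-UE on baseline FMA-UE, arm and marker, or by an arm-adjusted partial correlation.
- For baseline markers, add an arm-by-marker interaction, labelled exploratory and reported with its confidence interval.
- Describe adjusted slopes as association or prognosis only. When the marker is measured after treatment, do not read the arm coefficient in this model as the treatment effect.
- Limit candidate-selection wording to the interaction result, label it exploratory, and drop the claim about training intensity or dosage. Label any time-window statement observational.

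The cost is a change of wording and one regression per marker on data already to be collected. The drawback is that the interaction will be imprecise with about 60 patients, or fewer after fNIRS signal screening, so the selection claim becomes weaker.
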